# Study synopsis

| **Title of Study**  A Phase IIa, randomized, double-blind, placebo-controlled, exploratory, dose-ranging study to evaluate the safety, effectiveness and pharmacokinetics of three courses of DC-TAB treatment in patients with multiple sclerosis | |
| --- | --- |
| **Number of sites and countries**  5 sites/Bulgaria | |
| **Study period**  Start in Q2 2012 – Q4 2013 | **Phase of development**  IIa |
| **Objectives**  *Primary Objective*  To evaluate the safety and tolerability of three single doses of DC-TAB administered intravenously with 2-month intervals in patients with multiple sclerosis.  *Secondary objectives*   1. To evaluate the antigen-specific T-cell tolerance inducting effect of three single doses of DC-TAB administered intravenously with 2-month intervals in patients with multiple sclerosis. 2. To evaluate the clinical effects of three single doses of DC-TAB with 2-month intervals administered intravenously in patients with multiple sclerosis. 3. To evaluate the pharmacokinetics of DC-TAB in patients with multiple sclerosis. 4. To evaluate the effect of DC-TAB on levels of serum antibodies against CRYAB/DC-TAB | |
| **Methodology**  This study is a randomized, double-blind, placebo-controlled, exploratory, dose-ranging Phase IIa study to evaluate the safety, tolerability, T-cell tolerance inducing effect, clinical effects and pharmacokinetics of human alpha B-crystallin (CRYAB), the active ingredient of DC-TAB.  At entry patients will be randomized to one of the treatments, placebo, 7.5 mg DC-TAB, 12.5 mg DC-TAB or 17.5 mg DC-TAB in a 1:1:1:1 fashion. Patients will receive a single intravenous bolus injection which will be repeated twice with two month intervals during the 6-month monitoring period. Following a single intravenous bolus administration of DC-TAB, a state of T-cell tolerance is expected to be established within days.  The study consists of two parts, a treatment period of 24 weeks and a follow up period of an additional 24 weeks. Patients will return to the hospital weekly during the first month, and monthly thereafter.  The primary analysis will be performed on the treatment period, i.e. after all patients have completed 24 weeks; an additional analysis will be performed once all patients have completed the study. Patients and site study personnel will remain blinded throughout the study.  After 12 and 24 patients have completed 4 and after 24 patients have completed 12 weeks of follow-up a partially blinded safety review will be conducted by an independent DSMB to verify safety of the intervention in MS patients. | |
| **Number of patients planned**  32 patients are planned to be randomized (8 per treatment arm) | |
| **Diagnosis and main criteria for inclusion or exclusion**  Main inclusion criteria:   - Clinically definite, relapsing multiple sclerosis, according to the McDonald criteria, and abnormal MRI scan consistent with MS - Neurologically stable - At least one clinical relapse over the previous year, or two relapses over the past two years, or one or more gadolinium-enhancing MRI lesion(s) at the time of screening. - An EDSS score ≤ 5.5 - Age 18-55 years   Main exclusion criteria:   - Primary progressive multiple sclerosis - Systemic corticosteroid treatment for at least 3 consecutive days less than 30 days before screening - Plasmapheresis, or intravenous gammaglobulins less than 2 months before screening - Treatment with natalizumab less than one year before screening - Previous immunosuppressive treatment (e.g. cyclophosphamide or mitoxantrone) - Previous treatment with any leukocyte-targeting monoclonal antibody (e.g. rituximab, alemtuzumab, daclizumab) - Previous treatment with oral immune-modulatory agents (cladribine, fingolimod, laquinimod, fumarate)   Note: other current disease-modifying agents such as interferon-beta or glatiramer acetate are expected to not interfere with the intervention and are therefore allowed. | |
| **Test product, dose and mode of administration**  The investigational product, DC-TAB, is a sterile solution of highly purified recombinant human alpha B crystallin (CRYAB) at 12.5 mg/mL in phosphate-buffered saline, pH 7.2.  The intervention includes a single intravenous bolus injection repeated twice at 2-month intervals. Three different dose levels of DC-TAB will be evaluated:  Low dose: single dose of 7.5 mg  Intermediate dose: single dose of 12.5 mg  High dose: single dose of 17.5 mg  Patients will receive three courses of a single bolus injection of DC-TAB in this study. | |
| **Duration of treatment**  Single dose, repeated every 2 months. | |
| **Reference therapy, dose and mode of administration, batch number**  Phosphate-buffered saline (PBS) will be used as a placebo/reference.  It will be administered intravenously in the same volume and in the same manner as DC-TAB. | |
| **Criteria for evaluation** | |
| **Effect parameters**   - - Proliferative CD45RO+ (memory) and CD4+ (helper) T-cell response to DC-TAB   - New or enlarging gadolinium-enhancing lesions on T1-weighted MRI   - Clinical relapse   - EDSS   - MSIS-29   **Effect endpoints**   - T-cell responses (CD4+ and CD45RO+) to DC-TAB throughout the 48-week study - Cumulative number of new or enlarging gadolinium-enhancing MRI lesions between weeks 4 and 24 and between weeks 4 and 48 after treatment, relative to baseline - The number of clinical relapses between week 0 and week 24, and week 0 and week 48 - Change in EDSS score between week 0 and week 24, and week 0 and week 48 - Change in MSIS-29 score between week 0 and week 24, and week 0 and week 48 - Level of CRYAB/DC-TAB-reactive serum antibodies | |
| **Safety parameters**   - Number and frequency of adverse events (including local tolerability) - ECG parameters - Clinical chemistry and hematology parameters - Urinalysis - Vital signs and body temperature - MRI signs and symptoms | |
| **Pharmacokinetic parameters**   - AUC_0-24h_ - AUC_0-∞_ - C_max_ - t _1/2_ - t _max_ - Kel | |
| **Statistical methods**  **Statistical analysis methods**  The primary analysis will be done on the treatment period, i.e. once all patients completed the 24 week timepoint. An additional analysis will be performed at week 48.  Safety population  The safety population will comprise of all patients who received at least one dose of treatment.  Full analysis population (FAS)  The full analysis set (FAS) consists of all patients who received at least one dose of treatment and in whom at least one effect assessment is available beyond baseline.  Sample size  Since this is the first study in patients with MS the sample size is based on medical and practical grounds rather than statistical grounds.  Safety parameters  No formal statistics will be employed   - Adverse events (AEs) will be coded and presented using MedDRA. The overall incidence, the incidence of related as well as the incidence of serious adverse events (SAEs) will be summarized per dose and by body system in tables. - Local tolerability will be presented by overall incidence by treatment group per symptom. - Vital signs (supine blood pressure and heart rate) and body temperature: Descriptive statistics (n, mean, standard deviation, median, minimum, and maximum) will be provided for blood pressure, heart rate and body temperature and for changes from baseline. - Hematology, biochemistry and urinalysis parameters: Descriptive statistics (n, mean, standard deviation, median, minimum, and maximum) will be provided on values at baseline and all post-dose assessments. Descriptive statistics will be calculated on the change from baseline values. Out-of-normal-range values will be indicated for each parameter. The change in out-of-normal-range values after administration and at follow up versus baseline will be summarized per group by means of shift-tables. - ECG: Descriptive statistics (frequency, mean, standard deviation, median, minimum, and maximum) on ECG parameters will be provided at baseline and at all post-baseline assessments. Changes from baseline values will be calculated and descriptive statistics will be computed. Shift tables will also be provided to indicate changes in ECG parameters over time.   PK parameters  Descriptive statistics (n, mean, standard deviation, median, minimum, and maximum, plus Geometric mean and CV for C_max_ and AUC and the derived parameters) will be provided for the PK parameters.  Evaluations of dose-proportionality and effects of multiple dosing will be performed.  Effect parameters  Descriptive statistics (n, mean, standard deviation, median, minimum, and maximum) at each visit will be provided for all effect parameters and as well as change from baseline (n, mean, standard deviation, median, minimum, and maximum).  A Student’s T-test will be performed to analyze the changes in the absolute percentage of proliferated T-cells and of the cell division index over time.  Details on the analysis methods to be used for other effect parameters will be specified in the statistical analysis plan. | |

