## Study rationale and risk/benefits

### Study rationale

This study is designed to evaluate the safety and pharmacokinetics of three different dose levels of intravenous DC-TAB. DC-TAB is given as a single dose and repeated twice with a 2-month interval. In addition, the effects of the treatment on the development of MRI lesions, on T-cell tolerance, and on levels of CRYAB/DC-TAB-reactive serum antibodies will be explored.

DC-TAB aims to selectively suppress the activity of potentially pathogenic T cells reactive to CRYAB in the circulation of MS patients. Based on Phase I data in healthy subjects, as discussed above, it is expected that suppression of peripheral T-cell reactivity to CRYAB can be achieved by a single intravenous administration of DC-TAB, repeated with 2 month intervals. Induction of inducible, antigen-specific regulatory FoxP3^+^ T cells is the most likely mechanism involved. Once CRYAB-reactive T-cell responses are suppressed, it is expected that new inflammatory demyelinating MS lesions will no longer develop for a certain period. Due to the limited telomer length of inducible regulatory T cells in humans, however, their life span is likely limited to a few months only. For this reason, re-emergence of a CRYAB-specific T-cell response after treatment is likely to graduallybecome manifest again after 2-3 months. It is an important goal of the study to clarify, the dynamics of such a recovery of the T-cell response in MS patients.

The current protocol for tolerance induction in a Phase II study is based on the Phase I data. Although there are no *a priori* reasons, nor any experimental data to suggest that tolerance induction in MS patients is regulated any different from that in healthy subjects, the dose level required for optimal tolerance induction, and the persistence of the tolerant state, does require verification in MS patients prior to embarking on a larger study in MS patients. Also the safety of the intervention, notably including repeated administration with 2-month intervals, needs to be established in MS patients.

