# Investigational plan

## Overall study design and plan – description

This study is a randomized, double-blind, placebo-controlled, exploratory, dose-ranging Phase IIa study to evaluate the safety, tolerability, T-cell tolerance inducing effect, clinical effects, pharmacokinetics, and effects on serum antibodies of human alpha B-crystallin (CRYAB), the active ingredient of DC-TAB.

Patients who fulfill all eligibility criteria will be randomized to one of the treatments, placebo, 7.5 mg DC-TAB, 12.5 mg DC-TAB or 17.5 mg DC-TAB in a 1:1:1:1 fashion. Patients will receive a single i.v. bolus injection treatment which will be repeated twice with 2-month intervals during the 6-month monitoring period. By a single intravenous bolus administration of DC-TAB, a state of T-cell tolerance is expected to be established within days. Each month, T-cell responses to DC-TAB will be assessed (the results of which will be known two weeks after blood sampling). The interval period between treatments may be adjusted in case the duration of the tolerizing effect in patients is different from what is currently expected.

The study consists of two parts, a treatment period of 24 weeks and a follow up period of an additional 24 weeks. Patients will return to the hospital weekly during the first month, and monthly thereafter.

The primary analysis will be performed on the treatment period, i.e. after all patients have completed 24 weeks; an additional analysis will be performed once all patients have completed the study. Patients and site study personnel will remain blinded throughout the study.

After 12 and 24 patients have completed 4 and 12 weeks of follow-up, a partially blinded safety review will be conducted by the DMC to verify safety and adequate tolerization by the intervention in MS patients.

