## Selection of doses in the study

Based on Phase I data on the T-cell tolerizing effect of a single intravenous administration of DC-TAB, the effective dose in MS patients is expected to be approximately 0.2 mg/kg, or a fixed dose of approximately 12.5 mg per injection.

The NOAEL observed in rats following 28 days treatment was set at 17.5 mg/kg, which is equivalent to an HED of 3.2 mg/kg.

The NOAEL in female dogs could not be established following 15 days of treatment, whereas the NOAEL established for male dogs was 0.5 mg/kg following 15 consecutive dose administrations. The NOAEL for up to 5 days treatment was set at 12 mg/kg for both female and male dogs.

In healthy volunteers, single doses as well as three consecutive daily intravenous doses up to 37.5 mg were well tolerated and safe. Most commonly noted adverse drug reactions were local irritability and thrombophlebitis at the injection site.

In healthy volunteers, a single dose of 12.5 mg induced a statistically significant suppression of CD4+ and CD45RO+ T-cell responses to DC-TAB, in half the subjects to levels considered to reflect non-responsiveness. This immunological effect is expected to provide a clinical effect in MS patients. Suppression of T-cells was established within 8 days and maintained for 28 days, but had partially reversed after 6-8 months. In addition to the selection of 12.5 mg, one dose level above 12.5 mg (i.e. 17.5 mg) and one dose level below 12.5 mg (i.e. 7.5 mg) was selected for this study to further obtain information on the optimal dose. Given the currently information on the half-life of inducible regulatory T cells, the tolerizing effect is expected to be maintained for approximately 2-3 months after dosing. Therefore, dosing is repeated twice with 2-month intervals.

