### Effect data

Continuous variables will be summarized descriptively providing, where applicable, the number of patients (N), mean, standard deviation (SD), coefficient of variation, median, minimum (min) and maximum (max).

Changes from baseline will be summarized descriptively providing, where applicable, the number of patients (N), mean, standard deviation (SD), median, minimum (min) and maximum (max).

A Student’s T-test will be performed to analyze the changes in the absolute percentage of proliferated T-cells as well as the cell division index over time.

Details on the statistical analysis methods used will be further detailed in the statistical analysis plan.

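### The only T-cell test the protocol fixes is a Student's t-test of change over time, with no comparator and no dose term, which fits a dose-ranging aim badly

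*Protocol*

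**What the plan says.** The title in the synopsis describes a "randomized, double-blind, placebo-controlled, exploratory, dose-ranging study". Section 4.1 assigns patients to "placebo, 7.5 mg DC-TAB, 12.5 mg DC-TAB or 17.5 mg DC-TAB in a 1:1:1:1 fashion", and the synopsis plans 32 patients, 8 in each arm.

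The dose aim is explicit in two further places. Section 1.6.1 (Study rationale) says that "the dose level required for optimal tolerance induction, and the persistence of the tolerant state, does require verification in MS patients". Section 5.2 says that one dose level above and one below 12.5 mg "was selected for this study to further obtain information on the optimal dose".

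For the T-cell response, the Statistical methods part of the synopsis (Effect parameters) names a Student's t-test "to analyze the changes in the absolute percentage of proliferated T-cells and of the cell division index over time". Section 10.3.4 (Effect data) repeats it: "to analyze the changes in the absolute percentage of proliferated T-cells as well as the cell division index over time". Neither place says whether the test is paired or between groups, which groups are compared, or how dose enters. Descriptive statistics by visit and for change from baseline are planned as well.

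The two places differ in what they leave to the SAP. The synopsis defers the methods for the other effect parameters, which leaves the T-cell test fixed in the protocol. Section 10.3.4 says more broadly that the methods will be detailed further there. Methods that look across dose levels are named only for pharmacokinetics: dose-proportionality in the synopsis and analysis of variance in section 10.3.3.

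**The concern.** A t-test compares two groups or two time points. It takes no account of the ordering of four arms, and an arm-by-arm version discards the information shared by the 24 patients on active drug. For the secondary endpoint most closely tied to the dose question, the named inference therefore does not address the question that the dose arms were added to inform.

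If arm-by-arm results were read as evidence about dose, a pattern such as significant at 12.5 mg but not at 7.5 or 17.5 mg would look informative. Yet a difference in significance between two arms of 8 is not evidence of a difference between doses. Section 10.5 expects the study to give enough information on effect to start a Phase 2b study, so such a pattern could carry forward.

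**Working it through.** **Inputs.** From the protocol: four arms in equal allocation, 8 patients per arm, 4 × 8 = 32. The sample size rests on non-statistical grounds (section 10.5), so there is no power calculation to reproduce. The protocol gives no alpha, sidedness, effect size or SD, and its Phase I T-cell result is stated without a mean or SD. Assumed here: two-sided 5% per test, normal change scores with a common SD, no dropout, and the same true effect d (in SD of the change) in all three doses. Results are shown over d = 0.5 to 2.0.

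**Power of one arm's test.**
- Against placebo: noncentral t with 14 df and noncentrality d × √(8/2) = 2d.
- Paired within arm: noncentral t with 7 df and noncentrality d × √8 = 2.83d.

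**Chance of a split**, meaning that one or two of three equally effective doses reach significance.
- Within arm, the three tests are independent, so with power p the chance is 1 − p³ − (1 − p)³. At d = 0.5, p = 0.232 and 1 − 0.0125 − 0.453 = 0.53. At d = 0.8, p = 0.496 and the result is 0.75, which is the maximum of this formula.
- Against placebo, the tests share the placebo arm and are correlated, so the chance was simulated (200,000 trials).

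| d (SD) | Power, dose v placebo | Split, v placebo | Power, within arm | Split, within arm |
|---|---|---|---|---|
| 0.5 | 0.15 | 29% | 0.23 | 53% |
| 0.8 | 0.32 | 44% | 0.50 | 75% |
| 1.0 | 0.46 | 50% | 0.68 | 65% |
| 1.25 | 0.64 | 46% | 0.86 | 37% |
| 1.5 | 0.80 | 34% | 0.95 | 14% |
| 2.0 | 0.96 | 9% | 0.998 | 0.7% |

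**One model with all four arms** (pooled error, 32 − 4 = 28 df; a baseline covariate takes one more and changes little).
- Pooled active versus placebo: noncentrality d / √(1/8 + 1/24) = 2.45d. Power is 0.47 at 0.8 SD and 0.66 at 1.0 SD, against 0.32 and 0.46 for a single-dose t-test against placebo.
- Linear contrast in mg, when the true response is linear in dose: power 0.52 against 0.46 for top dose versus placebo if the top-dose effect is 1.0 SD, and 0.86 against 0.80 if it is 1.5 SD.
- A direct F test among the three active doses separates equal doses in 5% of trials, its nominal rate.
- The 95% interval for a difference between any two arms has half-width 2.048 × √(2/8) = 1.02 SD.

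**The case against.** **Detail belongs in the SAP.** Section 10.3.4 promises further detail there, and contrasts are routine SAP content. This stands in part: a dose-response analysis may exist in a SAP that is not at hand, so its absence from the trial is not shown. What remains is that the protocol fixes a particular test for this endpoint, the synopsis leaves only the other effect parameters open, and the fixed test does not match the stated aim.

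**No rule says that p-values choose a dose.** This stands. A reader might infer that doses will be labelled as working or not working by arm-wise significance, or that the trial is to pick the Phase 2b dose that way. Nothing in the protocol says so. Safety is the primary objective, the effect endpoints in section 10.1.2 are headed exploratory, and descriptive summaries will also inform the view of dose. The split percentages therefore describe a risk under one use of the results, not a planned decision.

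**The form of the test is open.** A reader might take it to be a two-sample test. The text speaks only of change over time, which fits a paired test at least as well.

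**The effect sizes are assumptions.** Splits are most frequent near 0.8–1.0 SD and become rare at 2.0 SD, so it cannot be said without qualification that equal doses will often be split.

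**A better model does not solve the dose question.** This stands too. The pooled contrast asks whether the drug does anything, not which dose is best. The gain from a linear contrast is modest and depends on the shape. A maximum test over a linear and a peaked shape showed no clear gain over the best single-arm t-test against placebo: power 0.59 against 0.59 for a rising response (0.5, 0.83, 1.17 SD) and 0.43 against 0.46 for a peaked one (0.5, 1.0, 0.5 SD), with the t-test unadjusted for picking the best arm. It is a matter of preference and is not recommended here.

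**Conclusion.** The point holds as a mismatch between a stated aim and a fixed method. The study is presented as dose-ranging, and the only T-cell inference written into the protocol ignores dose and names no comparator. A four-arm model raises the power to detect any drug effect from 32% to about 47% at 0.8 SD and from 46% to 66% at 1.0 SD, relative to a single-dose t-test against placebo. It also allows doses to be compared directly.

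These sizes rest on the assumed effects, two-sided 5% tests, equal effects across doses, normality, a common variance and complete data. The limit on telling doses apart comes mainly from 8 patients per arm, which no analysis removes. Because the endpoint is secondary and the study exploratory, this is a change that should be made, not a defect that invalidates the trial.

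**What to change.** In the synopsis (Effect parameters) and in section 10.3.4, replace the t-test sentence by one linear model of the change from baseline in the T-cell measure, with all four arms as groups and the baseline value as covariate. Pre-specify a pooled active-versus-placebo contrast, and a linear contrast in mg labelled exploratory. Report every dose-versus-placebo and dose-to-dose difference with a 95% interval, and state that doses are not ranked by arm-wise p-values.

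The cost is a few lines of wording and code, with no added patient, visit or sample. The wording should be settled before unblinding, since contrasts chosen afterwards are not credibly pre-specified. The downsides are the assumption of a common variance across arms, and intervals of about ±1.0 SD that will still not separate neighbouring doses well.
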